### **Methods for handling missing data**

Multiple imputation using chained equations will be used to account for missing data. The imputation model will use auxiliary variables gathered from routine AOANJRR data (including age, sex, baseline health, pain and function, diagnosis and surgical factors), as well as cluster and period effects. One hundred datasets will be imputed at the patient level, then each dataset will be analysed using the main analysis method with cluster summaries and combined using Rubin's rules. If there is any possibility of bias due to perfect prediction of rare outcomes such as VTE [27] or imputing values out of range for bounded variables such as pain scores or EQ5D [28], multiple imputation using chained equations will not be performed. Since the most likely reason for loss to follow-up is difficulty in contacting patients postoperatively (rather than association with treatment assignment or outcome), missing data will be assumed to be missing at random.

As a further sensitivity analysis for the primary outcome only, inverse probability weighting, where the complete cases are weighted by the inverse probability of being complete case will also be used to account for missing data. Inverse probability weighting has an advantage over multiple imputation when there are large blocks of missing data with either observed values for all variables or missing values for the majority of the variables, for example, pre-operative pain and function scores [29]. The inverse probability weights will be used to produce weighted cluster summaries, which will be analysed using the main analysis method, with cluster sizes calculated as the sum of the inverse probability weights.

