### **3.15. Statistical analysis**

The analysis for the primary objective will be limited to patients undergoing elective primary THA or TKA for a diagnosis of OA, excluding patients for whom the study drugs were contraindicated (e.g., allergy or need for alternative anticoagulant – warfarin, NOAC, dual antiplatelet, for a pre-existing condition). This analysis will test between-group difference in the proportion of cases developing VTE within 90 days for non-inferiority of aspirin at a margin of 1%, on an intention to treat basis.

The primary analysis will use cluster summary methods. These methods estimate the treatment effect using cluster level differences and have been shown to be appropriate for cluster randomised crossover trials with rare outcomes and the intracluster and interperiod correlation coefficients expected in this trial.

Multiple imputation to account for missing outcome data will be investigated, using auxiliary variables gathered from routine AOANJRR data (including age, sex, baseline health, pain and function, diagnosis and surgical factors). Since VTE is rare, if prediction in the imputation models using these auxiliary variables is a problem, no imputation will be performed due to the possibility of bias. Since the most likely reason for loss to follow-up is difficulty in contacting patients postoperatively (rather than any association with treatment assignment or outcome), missing outcome data is expected to be missing completely at random, which will not cause bias in the estimates.

Secondary analyses will be performed for the primary outcome, to test for differences in treatment effect between subgroups of patients: THA only, TKA only and bilateral joint replacement. The analysis method will be the same as the primary outcome and will include an interaction term between subgroup and treatment group.

Further secondary analyses will include an extension of the primary analysis for patients undergoing all forms of HA and KA (total, revision, partial) for any indication (non-elective surgery, non-OA diagnoses) and will include patients for whom the study drug was

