### **Intervention**

Each hospital (cluster) was allocated to consecutive periods of a standard protocol of LMWH and a standard protocol of aspirin as VTE prophylaxis, with the order being randomised. Patients in the aspirin group received aspirin at 85-150mg once daily, orally for 35 days post HA and for 14 days post KA, commencing within 24 hours of surgery. Patients in the LMWH group received enoxaparin at 40mg once daily, subcutaneously for the same time periods, with this dose reduced to 20mg for patients who weigh less than 50kg and for patients with an estimated glomerular filtration rate (eGFR) of less than 30mL/min who are not on dialysis. Other interventions that were standard across all sites were the intra- and post-operative use of intermittent pneumatic compression (IPC) calf devices until patients are mobile, the use of compression stockings, and mobilisation offered on day 0 or day 1 postoperatively.

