### ***Methods used for Interim Analyses***

Interim analyses were conducted for VTE and mortality within 90 days for population 1. To account for unequal cluster sizes, incomplete crossover or clusters which had not yet crossed over, a composite analysis was designed. For clusters which had crossed over, including with partial completion of the second period, the cluster weighted estimator intended for the primary outcome was used. Harmonic mean weighting when there are unequal cluster sizes has been shown to improve precision and 95% confidence interval coverage compared with unweighted or inverse variance estimates [25, 26]. Clusters which had not crossed over were analysed using the cluster period summaries, weighted by cluster size, in a parallel design approach, i.e., as if it were a cluster randomised trial without crossover. Estimates for the two approaches were combined using inverse variance weights to provide a final estimate. Confidence intervals were constructed using the Haybittle-Peto boundary of 0.001.

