## MAIN ANALYSES

The main analyses will include the primary and secondary outcomes for registered patients eligible to receive the study drug undergoing THA or TKA for a diagnosis of OA (population 1). In addition, the primary and secondary outcomes will be analysed for populations 2, 3 and 4. Mortality will also be analysed for population 5 (see “Additional analyses” below).

For the primary outcome, the analysis will test the between-group difference of cases developing a symptomatic VTE within 90 days for non-inferiority of aspirin at a margin of 1%. Cluster summary methods will be used to estimate the treatment effect using cluster level differences. These have been shown to be appropriate for cluster-randomised crossover trials with rare outcomes, and the intracluster and interperiod correlation coefficients expected in this trial. The crossover difference per cluster is the mean outcome for the intervention period minus the mean outcome for the control period. In a linear regression of cluster differences on treatment sequence, the treatment effect estimate is the intercept. To account for potential unequal cluster sizes, a cluster size weighted estimator will be used with harmonic mean weights of the number of patients in the two periods, which was the same method used in the interim analyses for incomplete crossover [25, 26]. Treatment effects will be presented as absolute risk differences and 95% confidence intervals will be examined to determine whether the non-inferiority margin has been met and whether superiority of one drug can be concluded. The primary outcome will be presented in Table 3 and Figure 4 will be used to demonstrate whether the non-inferiority margin has been met for the population 1 [30].

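### The imputation model as listed names neither treatment nor a cluster-by-period term; fitted as main effects, it would shrink the aspirin–LMWH difference by the fraction of outcomes missing

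*Supplement*

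**What the plan says.** - **Imputation model.** The final SAP, *Methods for handling missing data*, plans chained-equations multiple imputation from registry variables, and the list ends "pain and function, diagnosis and surgical factors), as well as cluster and period effects". It does not say whether these effects are main effects or crossed, or fixed or random.
- **Analysis of the imputed data.** A hundred datasets are imputed at patient level; "each dataset will be analysed using the main analysis method with cluster summaries and combined using Rubin's rules".
- **Estimator.** *Main analyses*: "In a linear regression of cluster differences on treatment sequence, the treatment effect estimate is the intercept".
- **Allocation.** *Intervention*: "Each hospital (cluster) was allocated to consecutive periods of a standard protocol of LMWH and a standard protocol of aspirin", in randomised order.
- **Hospitals with one period only.** *Methods used for Interim Analyses*, carried over to the final analysis: "Clusters which had not crossed over were analysed using the cluster period summaries, weighted by cluster size, in a parallel design approach". The two estimates are then combined by inverse variance.
- **Cancel rule.** "If there is any possibility of bias due to perfect prediction of rare outcomes such as VTE", or of imputed values falling outside a bounded scale, chained-equations imputation is not run. Protocol 3.15 has a similar clause: "no imputation will be performed due to the possibility of bias".
- **Second method.** "As a further sensitivity analysis for the primary outcome only, inverse probability weighting" of the complete cases is also planned.

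**The concern.** An imputation model should contain the contrast that the analysis estimates. Here that contrast is aspirin minus LMWH within hospital. In a two-period crossover, treatment is the sequence-by-period interaction. A hospital effect and a period effect added together do not span it. A programmer who fits the listed terms as main effects would impute the aspirin-period and LMWH-period patients of one hospital from rates that differ only by a common period effect. The observed patients would show the treatment difference and the imputed ones would not.

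The resulting bias is toward zero. If aspirin is worse, which is the case a non-inferiority test guards against, that direction favours non-inferiority. It also works against concluding that either drug is superior, a conclusion *Main analyses* allows. The same model serves the patient-reported secondary outcomes, for which inverse probability weighting is not planned. Mortality comes from death-index linkage and is little exposed.

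**Working it through.** **1. The plan's own figures.** With 2.5% v 1.5%, one-sided 0.025 and 90% power, the two-proportion formula gives 4,117 per group. With ICC 0.01, interperiod correlation 0.008 and 31 clusters:

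m = 4,117 × (1 − 0.01) / [31 − 4,117 × (0.01 − 0.008)] = 4,075.83 / 22.766 = 179.03, rounded up to 180 per arm per cluster; 180 × 62 = 11,160. The registration target is 251 × 62 = 15,562. All agree with the SAP. The documents give no figure for the imputation itself.

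**2. Missing fraction f.** The observed fraction is not in the documents. Protocol 3.9 uses 17% and 27%. The SAP's *Power and sample size* treats 27% as a maximum that also covers unequal cluster sizes and drop-out, and expects a smaller actual loss. I add 10% as an assumption.

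**3. Expected value, main effects only, crossed-over hospital.** Take LMWH rate p, aspirin rate p + d, the same f in both periods, outcomes missing completely at random, no period effect and balanced sequences. Both periods are imputed at p + d/2. Completed rates:

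- aspirin: (1 − f)(p + d) + f(p + d/2)
- LMWH: (1 − f)p + f(p + d/2)
- difference: (1 − f)d

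A common period effect cancels in the regression on sequence. Equivalently, the 1-point margin acts as one of 1/(1 − f): 1/0.83 = 1.20 points at 17%, 1/0.73 = 1.37 at 27%.

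**4. Other readings.** With cluster-by-period effects, each cell is imputed from its own rate and the difference stays at 1.00 point. A hospital with one period and a fixed cluster effect is imputed from its own cell mean, so it also stays at 1.00; a random cluster effect would shrink it partly. If crossed-over hospitals carry weight w in the composite and cluster effects are fixed, the overall factor is 1 − wf. Neither w nor the number of uncrossed hospitals is given. At w = 1 and f = 0.27 the factor is 0.73; at an assumed w = 0.5 it is 1 − 0.135 = 0.865.

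**5. Simulation.** 31 hospitals, all crossed over, 251 per period, ICC 0.01, interperiod correlation 0.008, rates 2.5% v 1.5% (truth at the margin). Logistic imputation with fixed cluster effects, the cluster-difference regression and Rubin's rules; 400 runs, 20 imputations (the plan has 100). NI is the share of runs declaring non-inferiority, nominally 2.5%.

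| Missing | (1 − f) × 1.0 | No treatment term: mean, NI | Complete cases, same runs: NI | With treatment term: mean, NI |
|---|---|---|---|---|
| 10% | 0.90 | 0.91, 5.0% | 2.8% | 1.02, 4.0% |
| 17% | 0.83 | 0.83, 7.2% | 2.8% | 0.97, 4.5% |
| 27% | 0.73 | 0.72, 9.8% | 4.3% | 1.01, 3.0% |

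The Monte Carlo SE of an NI figure is √(0.025 × 0.975/400) = 0.8 points near nominal and √(0.098 × 0.902/400) = 1.5 points at 9.8%. The shrinkage is therefore firm and the error rates are approximate.

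**6. Would the cancel rule fire?** Assuming beta-distributed hospital rates at the same parameters:

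| Observed per hospital-period | Zero-VTE cells, mean of 62 | At least one such cell | At least one whole hospital with zero VTE |
|---|---|---|---|
| 180 | 8.9 | over 99% | about 75% |
| 251 | 6.1 | over 99% | about 56% |

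The crossed reading cures the shrinkage, but with fixed effects it would almost surely produce empty cells.

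**The case against.** A reader might infer that the SAP excludes treatment, so that imputed VTE outcomes must carry no treatment effect. The text does not support that. Hospital and period together determine allocation, so crossed effects carry it in full. The registry items are called auxiliary, which usually means additions to the analysis variables. The amendment log gives accounting for clustering as the reason for the sentence. The SAP is silent on treatment and does not rule it out.

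A reader might also add together shrinkage from imputation and loss of imputation. These are alternatives: if imputation is cancelled for VTE, nothing shrinks. Nor does cancellation leave only an unadjusted complete-case result, because inverse probability weighting is planned separately for the primary outcome and uses observed outcomes only. Perfect prediction by hospital also presumes fixed cluster effects.

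The strongest point concerns early stopping. Recruitment ended on a two-sided 0.001 boundary. Suppose that boundary tested a zero difference, aspirin was the worse arm (the documents do not disclose the direction), and the final estimate is still at least 3.29 SE. After 27% shrinkage the upper limit is at least 0.73 × 3.29 + 1.96 = 4.36 SE. It falls below 1 point only if the SE is under 1/4.36 = 0.23 points, while the planning SE is 1.0/(1.96 + 1.28) = 0.31. On those assumptions a false non-inferiority claim is remote. This lowers the stake for the primary decision. It does not protect the size of the reported difference, its interval or the secondary outcomes.

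**Conclusion.** The point holds conditionally. If the listed effects are fitted as main effects and imputation is run, the aspirin–LMWH difference in crossed-over hospitals is multiplied by about 1 − f: a true 1.0 point becomes 0.83 at 17% missing and 0.72–0.73 at the 27% ceiling. With the truth at the margin, false non-inferiority is then about 7% and 10%, against 2.8% and 4.3% for complete cases.

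This rests on outcomes missing completely at random, equal loss in both arms, all hospitals crossed over, and imputation feeding the reported result. The shrinkage is absent if treatment is included, if the effects are crossed, in uncrossed hospitals with fixed cluster effects, or if imputation is cancelled. Inverse probability weighting is unaffected.

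The cancel rule is a related weakness. It has no operational threshold, zero-event hospitals would probably trigger it for VTE, and no replacement imputation method is named. As written, the section leads either to a model that may be biased or, probably, to none.

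**What to change.** 1. State that the imputation model includes treatment group, entered under its masked label, or a cluster-by-period effect; or impute separately by treatment group. Apply this to primary and secondary outcomes alike.
2. State whether cluster effects are fixed or random.
3. Replace the cancel rule with an imputation method that tolerates sparse events and, for the scores, bounded ranges. The choice of method can be left to the trial statistician.

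The cost is a few sentences and minor code, with no new data. Masking is no obstacle, since the SAP's *Blinding* section already works with dummy group names and allows final amendments after the blind missing-data review, before database lock.

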### **Trial profile and baseline characteristics**

The flow of participating hospitals (including losses and exclusions) through the study and participating patients will be reported in line with the Consolidated Standards of Reporting Trials (CONSORT) statement (Figures 2 and 3).

Baseline characteristics of participating clusters, including number of annual HA and KA procedures performed in the year prior to trial commencement, hospital type (public or private hospital), initial treatment allocation and whether the hospital achieved crossover are shown in Table 1. This table also shows the number of patients registered for population 1 (the population used for the sample size calculation) by each participating hospital and the overall registration rate of each hospital will be presented as outlined. The overall registration rate describes the number of registered patients undergoing any HA or KA procedure (population 4) divided by the number of patients who underwent any HA or KA procedure over the duration of the trial at participating hospitals (regardless of whether they were registered – population 5). Hospital names will remain anonymous.

Descriptive statistics of baseline patient characteristics for all registered patients eligible to receive the study drug (population 3) will be presented by prophylaxis group (Table 2).

**Figure 2.** Flowsheet of participating hospitals

[figure not shown]

**Figure 3.** Flowsheet of patients within population 1†

[figure not shown]

† Population 1 refers to registered patients undergoing primary THA or TKA for a diagnosis of OA, who are eligible to receive the study drug

**Table 1.** Number of registered patients for population 1† by treatment group and overall registration rate for each participating hospital

| Hospital     | Number of HA and KA Procedures performed (2018) | Insurance Status | Initial Treatment Allocation | Crossover Achieved | LMWH Group (Population 1) | Aspirin Group (Population 1) | Overall Registration Rate (combined for both groups) |
|--------------|-------------------------------------------------|------------------|------------------------------|--------------------|---------------------------|------------------------------|------------------------------------------------------|
| 1            |                                                 |                  |                              |                    | n                         | n                            | %                                                    |
| 2            |                                                 |                  |                              |                    | n                         | n                            | %                                                    |
| 3            |                                                 |                  |                              |                    | n                         | n                            | %                                                    |
| 4            |                                                 |                  |                              |                    | n                         | n                            | %                                                    |
| 5            |                                                 |                  |                              |                    | n                         | n                            | %                                                    |
| 6            |                                                 |                  |                              |                    | n                         | n                            | %                                                    |
| 7            |                                                 |                  |                              |                    | n                         | n                            | %                                                    |
| 8            |                                                 |                  |                              |                    | n                         | n                            | %                                                    |
| 9            |                                                 |                  |                              |                    | n                         | n                            | %                                                    |
| 10           |                                                 |                  |                              |                    | n                         | n                            | %                                                    |
| 11           |                                                 |                  |                              |                    | n                         | n                            | %                                                    |
| 12           |                                                 |                  |                              |                    | n                         | n                            | %                                                    |
| 13           |                                                 |                  |                              |                    | n                         | n                            | %                                                    |
| 14           |                                                 |                  |                              |                    | n                         | n                            | %                                                    |
| 15           |                                                 |                  |                              |                    | n                         | n                            | %                                                    |
| 16           |                                                 |                  |                              |                    | n                         | n                            | %                                                    |
| 17           |                                                 |                  |                              |                    | n                         | n                            | %                                                    |
| 18           |                                                 |                  |                              |                    | n                         | n                            | %                                                    |
| 19           |                                                 |                  |                              |                    | n                         | n                            | %                                                    |
| 20           |                                                 |                  |                              |                    | n                         | n                            | %                                                    |
| 21           |                                                 |                  |                              |                    | n                         | n                            | %                                                    |
| 22           |                                                 |                  |                              |                    | n                         | n                            | %                                                    |
| 23           |                                                 |                  |                              |                    | n                         | n                            | %                                                    |
| 24           |                                                 |                  |                              |                    | n                         | n                            | %                                                    |
| 25           |                                                 |                  |                              |                    | n                         | n                            | %                                                    |
| 26           |                                                 |                  |                              |                    | n                         | n                            | %                                                    |
| 27           |                                                 |                  |                              |                    | n                         | n                            | %                                                    |
| 28           |                                                 |                  |                              |                    | n                         | n                            | %                                                    |
| 29           |                                                 |                  |                              |                    | n                         | n                            | %                                                    |
| 30           |                                                 |                  |                              |                    | n                         | n                            | %                                                    |
| 31           |                                                 |                  |                              |                    | n                         | n                            | %                                                    |
| Total |                                                 |                  |                              |                    | n                  | n                     | %                                             |

† Population 1 refers to registered patients undergoing primary THA or TKA for a diagnosis of OA, who are eligible to receive the study drug

**Table 2.** Baseline patient characteristics for all registered patients eligible to receive study drug (population 3), according to treatment allocation

|                                 | LMWH
(n = X) | Aspirin
(n = X) |
|---------------------------------|------------------------|---------------------------|
| Age (years)                     | xx.x (xx.x – xx.x), n  | xx.x (xx.x – xx.x), n     |
| BMI (kg/m  )        | xx.x (xx.x – xx.x), n  | xx.x (xx.x – xx.x), n     |
| Male sex                        | n (%)                  | n (%)                     |
| ASA Grading                     |                        |                           |
| 1                               | n (%)                  | n (%)                     |
| 2                               | n (%)                  | n (%)                     |
| 3                               | n (%)                  | n (%)                     |
| 4                               | n (%)                  | n (%)                     |
| 5                               | n (%)                  | n (%)                     |
| Previous venous thromboembolism | n (%)                  | n (%)                     |
| Long term anticoagulant use     |                        |                           |
| Aspirin                         | n (%)                  | n (%)                     |
| Other single antiplatelet       | n (%)                  | n (%)                     |
| Joint replacement               |                        |                           |
| THA                             | n (%)                  | n (%)                     |
| TKA                             | n (%)                  | n (%)                     |
| Other HA                        | n (%)                  | n (%)                     |
| Other KA                        | n (%)                  | n (%)                     |
| Bilateral                       | n (%)                  | n (%)                     |
| Type of surgery                 |                        |                           |
| Primary total                   | n (%)                  | n (%)                     |
| Primary partial                 | n (%)                  | n (%)                     |
| Primary resurfacing             | n (%)                  | n (%)                     |
| Revision                        | n (%)                  | n (%)                     |
| Other                           | n (%)                  | n (%)                     |
| Indication                      |                        |                           |
| Osteoarthritis                  | n (%)                  | n (%)                     |
| Inflammatory                    | n (%)                  | n (%)                     |
| Avascular Necrosis              | n (%)                  | n (%)                     |
| Fracture                        | n (%)                  | n (%)                     |
| Other                           | n (%)                  | n (%)                     |
| Prosthesis                      |                        |                           |
| Cemented                        | n (%)                  | n (%)                     |
| Hybrid                          | n (%)                  | n (%)                     |
| Uncemented                      | n (%)                  | n (%)                     |
| Pain and Function               |                        |                           |
| Oxford Hip Score                | xx.x (xx.x – xx.x), n  | xx.x (xx.x – xx.x), n     |
| Oxford Knee Score               | xx.x (xx.x – xx.x), n  | xx.x (xx.x – xx.x), n     |
| EQ-5D                           | xx.x (xx.x – xx.x), n  | xx.x (xx.x – xx.x), n     |
| EQ-VAS                          | xx.x (xx.x – xx.x), n  | xx.x (xx.x – xx.x), n     |

Abbreviations: *BMI* body mass index, *ASA* American society of anaesthesiologists

